## Abstract

**Background:**

South Africa has the largest HIV epidemic in the world; in KwaZulu-Natal Province, over 40.8% of adults aged 15 years and older are living with HIV. Despite this, South Africa is home to only 3% of the world’s health care workers. Nurses constitute the largest group of providers in South Africa and experience high levels of burnout, which can contribute to negative patient outcomes for people living with HIV, including reduced treatment adherence. Nurse-centered interventions that offset these effects are urgently needed.

**Objective:**

This study aims to test the feasibility and acceptability of an adapted resiliency intervention (Stress Management and Resiliency Training-Relaxation Response Resiliency Program) for professional nurses who provide care for people living with HIV in South Africa.

**Methods:**

In phase 1 (Human Research Ethics Committee [Medical] of the University of the Witwatersrand [220813, Johannesburg, South Africa] and the Massachusetts General Brigham Institutional Review Board [2022P002765, Boston, Massachusetts, United States]), we conducted 3 focus group discussions to solicit feedback on the lived experiences of stress, sources of stress, impact on job functioning, coping strategies, the proposed intervention, and recruitment strategies for nurses. These data informed adaptations to the intervention. In phase 2 (Human Research Ethics Committee [240106, Johannesburg, South Africa]; Massachusetts General Brigham Institutional Review Board [2024P001407, Boston, Massachusetts, United States]), we conducted a small proof-of-concept study (N=8) with preintervention and postintervention assessments, 6 intervention sessions with a nurse interventionist, and a qualitative exit interview. Following appropriate adaptations, we conducted a pilot randomized controlled trial (N=60) in which participants were randomized to the intervention or the control condition. The control condition received a one-time, 90-minute didactic stress management session. The intervention condition consisted of two 4-hour group skills-based sessions on the relaxation response, components of stress, recuperative sleep, mindful awareness, resilience, and social support. Sessions included practice-based exercises and videos to complement the intervention materials. Baseline, posttreatment (intervention only), and follow-up assessments, as well as qualitative exit interviews (n=15, intervention only), were conducted. Primary outcomes are feasibility (number screened, eligible, and enrolled; the number of treatment sessions and assessments completed in the intervention arm; assessment duration; and reasons for declining enrollment and prematurely leaving the trial) and acceptability (Client Satisfaction Questionnaire-8 and qualitative data).

**Results:**

The project is funded by the National Institute of Mental Health (R34MH126753; September 2022). As of October 2025, we have completed both the proof-of-concept study (n=8; February 2025) and the pilot randomized controlled trial (n=60; August 2025). Data analysis is in progress and is expected to be completed in August 2026.

**Conclusions:**

Structural changes are needed to ensure the well-being of health care providers; however, given that structural changes take time, money, and political capital to execute, we must develop interventions to support providers’ mental health while advocating for systematic change.

## Introduction

### Background

South Africa has the largest HIV epidemic in the world, with 7.9 million people infected and prevalence rates of 22.6% among females and 11.5% among males aged 15 to 49 years [1]. South Africa’s epidemic accounts for 19% of the global population of people living with HIV, 15% of new infections, and 11% of AIDS-related deaths worldwide [2]. KwaZulu-Natal Province is particularly affected; 40.8% of adults over age 15 years are living with HIV, and people living in this province have a 46% higher risk of infection than those outside the province [3]. South Africa has made considerable progress toward achieving the global 95-95-95 targets, but in 2023 only 83% of people living with HIV were on antiretroviral therapy (ART) and just 78% had suppressed HIV RNA [4]. Available interventions to support patient care engagement have not closed enough of the treatment gap, and innovative interventions to promote patient engagement are urgently needed, particularly those that support the needs of frontline providers, such as nurses.

Despite bearing nearly one-fifth of the global HIV burden, South Africa has only 3% of the world’s health care workers, a shortage caused by uneven geographical distribution of personnel, migration, and burnout [5,6]. Reported reasons for provider migration out of South Africa include dissatisfaction with pay, lack of advancement opportunities, and work-related stress [7-9]. Nurses constitute the largest group of health care providers in South Africa—81% of public sector health professionals in 2015 [10]. Yet, in 2019, there was an estimated shortage ranging from 26,000 to 62,000 nurses, and the shortage is expected to increase to 131,000 to 166,000 by 2030 [11]. Limited resources lead to overwhelming caseloads, resulting in burnout, low retention, chronic stress, hopelessness, and cynicism among nurses [9,12]. South African nurses are faced with chronic work overload and occupational stress [13-15], in part due to inadequate staffing, resources, and wages [9,14,16,17]. Since 2010, South Africa has increasingly adopted task-shifting as part of an effort to scale up its ART program; for nurses, this has meant an ever-greater task burden [18,19]. Household challenges can exacerbate work stressors, as the demands of nursing combined with traditional gender norms and family economic dependency contribute to chronic stress [20]. In a sample of South African hospital nurses, both personal and work-related stress were significantly associated with burnout [21]. Burnout—characterized by exhaustion, cynicism, and inefficiency—is a prolonged response to chronic emotional and interpersonal stressors [22] and is linked to job dissatisfaction and intention to leave [7,23].

Resource limitations and associated stress and burnout in nurses lead to negative patient outcomes that disrupt the HIV treatment cascade and compromise HIV outcomes. Patient engagement with HIV care (eg, attending appointments, adhering to ART, refilling prescriptions, managing side effects) is facilitated principally through nurse-patient relationships. Stress and burnout among nurses can negatively affect people living with HIV in a variety of ways, including (1) self-reported suboptimal care of and negative attitudes toward patients [24]; (2) decreased patient satisfaction [25,26]; (3) increased posthospitalization recovery time [26]; and (4) reduced ART adherence, HIV testing uptake, and prevention of mother-to-child transmission care due to experienced or anticipated negative provider interactions [27-29]. Patient perceptions of the patient-provider relationship are a core element of engagement and retention in HIV care [30,31]. Among first-time ART users, a strong patient-provider relationship has been found to be particularly important for maintaining adherence [32,33]; yet, patients have reported discrimination, stigmatization, and provider breaches of patient confidentiality at HIV clinics [34,35]. In general, patients prefer providers who have good communication skills and are empathetic, engaging, and validating [36]. These qualities build trust, which is positively associated with HIV care adherence [37]. When nurses who care for people living with HIV experience stress and burnout, patient-nurse relationships suffer and trust may be impacted; providers experiencing burnout report making treatment mistakes, yelling at patients, and rushing through diagnostic tests [38]. In South Africa, stress due to increased workload, staff shortages, and poor working conditions has been associated with nurse absenteeism [39], which further damages these relationships and cripples an underresourced health care system.

Even though HIV care nurses in South Africa experience particularly high levels of stress and burnout [9,13,14,16,40,41], there have been no systematic efforts to develop skills-based programs to help nurses manage and cope with the occupational-related and personal stressors that negatively affect patient outcomes. Stress reduction interventions have been used in a variety of medical settings across North America and have been found to decrease burnout and stress among nurses in oncology [42], pediatric intensive care units [43], and large health care organizations [44], as well as among nursing students [45]. In South Africa, an intervention that increases nurses’ resiliency may decrease stress, prevent burnout, and lead to improved patient engagement in HIV care and may be important to support nurse well-being. Resiliency is a “multidimensional construct that refers to the ability to maintain adaptation and effective functioning under significant adversity or challenging life conditions” [46], or stress. Skills that foster resilience include increasing social support, mastery (a sense of control over one’s life), optimism, acceptance, will to live, effective self-management, and generativity [47,48]. Resiliency interventions go beyond traditional stress management interventions by adding elements of positive psychology, which may teach individuals not only how to manage immediate stressors but also how to live purposefully, optimize health, and build “immunity” for better long-term stress management—key in this setting where widespread structural changes to decrease nurses’ stress are unlikely in the near future.

### Theoretical Framework

The stress response, or the “fight-or-flight” response, is a set of physical changes in the body in response to demands ranging from major negative life events to small daily challenges. The goal of the Stress Management and Resiliency Training-Relaxation Response Resiliency Program (SMART-3RP) is to decrease the physiological, emotional, cognitive, and behavioral effects of the stress response by promoting the physiological, emotional, cognitive, and behavioral effects of the relaxation response (RR) [46]. To achieve these goals, the SMART-3RP focuses on three major areas: (1) eliciting the RR, (2) increasing stress awareness, and (3) promoting adaptive strategies. Eliciting the RR involves learning strategies to reduce muscle tension, breathing rate, heart rate, and blood pressure, with the aim of helping to regulate the cellular responses to stress. Decreasing stress reactivity involves increasing one’s awareness of being in the stress response (negative thoughts, emotions, physical reactions, and behaviors) and learning skills to change or alter these components (eg, cognitive restructuring). Adaptive strategies focus on learning and using different techniques to promote positive growth and self-efficacy in response to stress. Given high levels of community stigma toward people living with HIV [35] and patients’ desire for providers who have good communication skills and are empathetic, engaging, and validating [36], adaptations to the SMART-3RP were made by adding stigma reduction and communication skills as adaptive strategies. The intervention was further adapted based on phase 1 focus group discussion (FGD) feedback [49]. It is the learning and integration of these 3 core elements that enables individuals to adaptively cope with stressful situations and thus increase resiliency. The SMART-3RP model has been adapted and refined to reflect additional clinician-patient dynamics and interdependence (Figure 1; novel components added to the model are indicated with an asterisk).

**Figure 1. F1:**
[figure not shown]
Overview of adapted Stress Management and Resiliency Training-Relaxation Response Resiliency Program model [46]. RR: relaxation response. ^a^Novel components added to the model.

### Study Aims

We aim to conduct a small proof-of-concept study (N=8) and a pilot randomized controlled trial (RCT; N=60) of the SMART-3RP, a skills-based intervention that has been tailored to enhance resiliency among professional nurses providing HIV care in the public sector in South Africa. We will test the feasibility and acceptability of all study procedures in preparation for a larger trial testing the efficacy and implementation strategies of the intervention. To assess feasibility, we tracked the number of participants screened, eligible, and enrolled; the number of treatment and assessment sessions completed; assessment duration; and reasons for declining enrollment and for prematurely leaving the trial. To assess acceptability, we used a measure of participant satisfaction and qualitative exit interview data. We hypothesize that the intervention and study procedures will be feasible and acceptable.

## Methods

### Adaptation of SMART-3RP Intervention

#### Focus Group Discussions

The first phase of this study collected formative, qualitative data via FGDs to inform the adaptation of the SMART-3RP for delivery to nurses providing HIV care in the public health sector in South Africa. The study was introduced to KwaZulu-Natal Provincial and eThekwini District health departments and to clinic managers and professional nurses from the selected clinics by study team members. Interested professional nurses were recruited from a public health care (PHC) facility in South Africa and were eligible if they (1) had provided HIV care in a public sector or partner organization health clinic at the level of professional nurse (ie, typically holding a Bachelor of Nursing degree and registration with the South African Nursing Council) for at least 12 months, (2) were able and willing to sign informed consent, and (3) were aged 18 years and older. A trained study team member without any supervisory power over the nurse interviewees facilitated 3 FGDs with a total of 14 nurse participants (one group of 4 and two groups of 5 participants each). FGDs lasted 50 to 90 minutes and were conducted in a private room.

A semistructured FGD guide (Multimedia Appendix 1) was developed by the study team based on a review of the existing literature and potential logistical issues that could impact intervention delivery. FGDs gathered information across three domains relevant to SMART-3RP intervention adaptation and implementation: (1) role of culture, perceptions, and experiences of stress; sources of stress (eg, occupational, trauma-related, structural); how stress impacts job functioning (specifically patient care); and current coping strategies; (2) recommendations about the intervention (eg, modules and content, number of sessions, session duration, program length, mode of delivery [virtual, in-person, hybrid approaches], and use of coaches); and (3) the most effective means to recruit professional nurses for a future clinical trial, including minimizing the possibility of coercion and ensuring nurses do not feel “blamed” for insufficient resilience. Most participants preferred an in-person, group format, believing this would enhance their interaction with one another as well as allow for open dialogue and deeper engagement with SMART-3RP material. Participants stressed the importance of (1) having an interventionist present to answer questions and facilitate engagement, (2) ensuring support from clinic management, which would communicate the value of the program to both staff and patients, and (3) normalizing discussions about stress. Participants were supportive of using texting platforms (eg, WhatsApp) to maintain connectedness with other participants and support ongoing skill use.

Changes to the content of the intervention were made based on the FGD results [49]. These included (1) integrating the normalization of stress and talking about stress, (2) discussing the importance of stigma awareness in patient care, (3) integrating an overview of practicing empathy and compassion in patient care while under high pressure, and (4) integrating examples with local imagery for relaxation exercises and adapting food and physical activity guidelines to match the guidelines for South Africa. Additionally, the intervention format was changed from 3 to 6, 1-hour each, in-person group sessions to accommodate the availability of staff to attend the sessions in the midst of a heavy workload and to avoid disrupting patient flow.

#### Proof-of-Concept Study

After conducting the FGDs and finalizing the study documents, we conducted a small proof-of-concept study (N=8) of the intervention, including baseline and posttreatment assessments, during which the adapted materials were simulated and tested. We conducted qualitative exit interviews (see Multimedia Appendix 2 for the interview guide) from 7 proof-of-concept study participants to explore their experiences in the study (eg, treatment content, length of sessions, scheduling/location of sessions, adherence to the skills covered in the sessions, and length of the overall intervention).

#### Refinement of the SMART-3RP Intervention

Additional changes were made to the intervention format and the protocol based on data from the proof-of-concept study and concurrent changes in health care delivery conditions in South Africa. Specifically, following the proof-of-concept study, South Africa experienced a large wave of layoffs among nurses providing care to people living with HIV due to reduced availability of funding that supports health care infrastructure in South Africa (eg, cuts to President’s Emergency Plan for AIDS Relief and US Agency for International Development); there was also concern that the grant would be terminated. To increase participant outreach and collect as much data as possible before a potential grant termination, the study team changed the format of the intervention to two 4-hour sessions and allowed for the participation of nurses who had recently been laid off but otherwise met the inclusion criteria.

### Pilot RCT

#### Characteristics of Study Population

We enrolled 60 professional nurses for the randomized pilot. Inclusion criteria were (1) having provided HIV care in a PHC facility (at the level of professional nurse) for at least 1 year; (2) being aged 18 years and older; and (3) being able and willing to sign informed consent. Exclusion criteria included participation in cognitive behavioral therapy and/or a mind-body intervention in the past year.

#### Recruitment and Enrollment

Participants were recruited from several PHC facilities (eg, primary health clinic, community health center, district hospital gateway clinic) and partner organizations that support the HIV program in the eThekwini District. By sampling from several PHC facilities in the eThekwini District of KwaZulu-Natal Province, we expected to recruit a representative sample of nurses providing HIV care in the primary health care sector. To identify eligible professional nurses, we consulted with KwaZulu-Natal Provincial Health Department managers, managers of partner organizations providing HIV care in eThekwini District, eThekwini District Health leadership, and PHC facility managers before the initiation of study procedures. Study participation was offered to all professional nurses meeting the inclusion criteria at each clinic until the target sample size was met.

#### Research Procedures

##### Informed Consent

A detailed informed consent form was reviewed with all participants by local study staff in a private setting. The consent form included an overview of all study procedures, information about potential risks and benefits of participation (including possible social harms associated with participation), and contact information of study team members.

##### Group Assignment

After completion of the small proof-of-concept study, the randomized pilot study (N=60 nurses) was conducted. Once participants were screened, they were asked to select their availability based on 4 possible dates, which were randomly assigned as intervention or control. The groups consisted of approximately 10 participants each.

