### Data Analysis

The sample size (N=60) was chosen based on studies of similar scope (eg, other pilot behavioral trials funded via the same mechanism) and established guidelines for pilot behavioral studies to establish feasibility [62-64].

To evaluate feasibility as a coprimary outcome, we will assess the number of nurse participants screened, eligible, and enrolled (ie, whether >70% of those screened enroll/agree to participate); the number of treatment sessions (ie, whether >70% of participants randomized to the intervention complete at least 2 out of 3 sessions) and assessment visits completed (ie, whether >70% of all participants complete at least 2 out of 3 assessments) in the intervention arm; assessment duration; and reasons for declining enrollment and prematurely leaving the trial. Acceptability (second primary outcome) will be evaluated using the Client Satisfaction Questionnaire (CSQ-8) [61] and qualitative exit interview data among intervention arm participants. Scores on the CSQ-8 will be categorized into 4 levels of satisfaction: ‘‘poor’’ (score 8‐13), ‘‘fair’’ (score 14‐19), ‘‘good’’ (score 20‐25), and ‘‘excellent’’ (score 26‐32). All qualitative exit interview data will be explored for categories and themes around intervention acceptability. Qualitative data will be analyzed using content analysis, facilitated by the Dedoose software [65], to organize data and facilitate analyses. Two study team members will independently review the transcripts to generate an overarching thematic framework for data interpretation, in which major and minor themes are identified. Thematic frameworks will then be compared for consistency, and discrepancies will be discussed until agreement is reached. Data will be reexamined, messages will be extracted and highlighted, and ongoing discussion between coders will allow for further theorizing and making interconnections between research questions, coding categories, and raw data [66].

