With respect to exploratory evaluations of quantitative data and secondary outcomes, we expect to compare each outcome between groups using mixed model regression analyses, with participant ID as a random effect. Fixed covariates will include assessment time point (baseline, posttreatment assessment, and 3-month follow-up) and years working in HIV care. Other covariates, such as education, age, and baseline levels of stress, anxiety, and depressive symptoms, and clinic characteristics (eg, clinic size, availability of equipment, and urban vs peri-urban) will also be considered. We will consider exploratory mediational and moderational analyses, based on procedures outlined by Hayes [67]. We will examine patterns in missing data to see if missingness is related to measured participant characteristics. We will adjust for missing data using multiple imputation, as appropriate. We will also adjust for multiple comparisons using the method of Hothorn et al [68].

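### Session dates were randomised, but the between-arm mixed model names only a participant effect, so exploratory standard errors may be too small

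*Protocol article*

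**What the plan says.** On allocation, the Group Assignment section of the protocol article says of the screened nurses that "they were asked to select their availability based on 4 possible dates, which were randomly assigned as intervention or control". It adds: "The groups consisted of approximately 10 participants each". The Methods part of the Abstract describes the same trial differently: "participants were randomized to the intervention or the control condition".

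On analysis, the Data Analysis section says of the exploratory and secondary outcomes: "we expect to compare each outcome between groups using mixed model regression analyses, with participant ID as a random effect". It continues: "Fixed covariates will include assessment time point (baseline, posttreatment assessment, and 3-month follow-up) and years working in HIV care". Of further covariates it says that "clinic characteristics (eg, clinic size, availability of equipment, and urban vs peri-urban) will also be considered". No term for session date or session group is named.

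On size, the same section says: "The sample size (N=60) was chosen based on studies of similar scope", together with guidelines for pilot studies. No ICC, design effect, significance level or allocation ratio is given.

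**The concern.** If dates are assigned to arms, all nurses on a date receive the same condition, and the design is a cluster allocation with very few clusters. A participant random effect handles repeated measurements on one nurse. It does nothing for correlation between nurses on the same date.

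Such correlation could arise in two ways:

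- **Before allocation.** Nurses indicated when they were available. They came from several facilities and partner organisations, and some had recently been laid off. Availability may go with workplace or employment status, and these may go with stress and burnout. The article does not show that this happened, but nothing in the allocation prevents it.
- **After allocation.** Intervention nurses shared two 4-hour group sessions and could join a WhatsApp group restricted to their cohort.

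At stake are the standard errors, intervals and p-values for the between-arm comparisons of stress, burnout, resilience and the other scales. The planned multiplicity adjustment controls error across several tests. It does not repair a standard error that is too small within each test.

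**Working it through.** **Plan's own figure.** N=60 was set by precedent and guidelines, so there is no formula to reproduce.

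**Inputs from the article.** 60 nurses, 4 dates, groups of about 10, and participant ID as the named random effect.

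**Assumed inputs.** Equal arms, two-sided 5%, ICC from 0 to 0.10, and clustering in both arms. Cluster size m is 60/4 = 15 if the date is the cluster, or 10 if correlation acts within session groups of the stated size (60/10 = 6 groups).

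**Formulas.** Design effect DE = 1 + (m − 1) × ICC. True SE / model SE = √DE. Actual type I error = 2 × [1 − Φ(1.96/√DE)].

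| m | ICC | DE | SE ratio | Type I error |
|---|---|---|---|---|
| 15 | 0 | 1.00 | 1.00 | 5.0% |
| 15 | 0.01 | 1 + 14 × 0.01 = 1.14 | 1.07 | 6.6% |
| 15 | 0.05 | 1 + 14 × 0.05 = 1.70 | 1.30 | 13.3% |
| 15 | 0.10 | 1 + 14 × 0.10 = 2.40 | 1.55 | 20.6% |
| 10 | 0.01 | 1 + 9 × 0.01 = 1.09 | 1.04 | 6.0% |
| 10 | 0.05 | 1 + 9 × 0.05 = 1.45 | 1.20 | 10.4% |
| 10 | 0.10 | 1 + 9 × 0.10 = 1.90 | 1.38 | 15.5% |

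Simulation of individual-level t tests (40,000 trials per setting) agreed within 0.01. A t test on cluster means held the error at 4.8% to 5.2%.

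If only the intervention arm is clustered, the variance inflation is (DE + 1)/2. For m = 15 and ICC 0.05 that is (1.70 + 1)/2 = 1.35, and the type I error is 9.2%.

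**Does the repeated-measures model rescue this?** The arm-by-time contrast was simulated with two time points, an assumed within-person correlation of 0.5 and a participant effect only.

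- *Group effect constant over time:* it cancels, and the arm-by-time error stays at about 5%. The arm main effect is still inflated, to 16% at ICC 0.05 with m = 15.
- *Group effect arising after baseline:* it does not cancel. The arm-by-time error is 6.7%, 13.8% and 21.1% (m = 15), or 6.3%, 10.1% and 15.7% (m = 10), at ICC 0.01, 0.05 and 0.10.

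**Degrees of freedom, whatever the ICC.** If the 4 dates split 2 v 2, a date-level comparison has 4 − 2 = 2 df and critical t 4.30, against 2.00 at 60 − 2 = 58 df. There are C(4,2) = 6 possible allocations, so the smallest two-sided randomisation p is 2/6 = 0.33.

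**Counts.** One group of about 10 on each of 4 dates gives 4 × 10 = 40. Reaching 60 needs about 15 per date, or more than one group on some dates.

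**The case against.** The strongest reply is that the affected comparisons are exploratory or secondary. The coprimary outcomes are feasibility and acceptability; none needs a between-arm test, and the satisfaction score and exit interviews concern the intervention arm alone. The article states no significance level, power or efficacy hypothesis. All of this stands. A reader might infer that the trial's main conclusions are undermined, or that between-arm p-values will decide the larger trial. The article supports neither: the Study Aims section says that the feasibility and acceptability of procedures are tested in preparation for that trial.

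A second reply is that the article condenses a fuller plan and does not say that participant ID is the only random effect. That is fair as to wording. But the article itself states both the allocation and a random-effect structure, and as stated they do not match. Clinic covariates, if used, may absorb some variation between clinics but do not represent the date.

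A third is that inflation is not certain. This also stands. A reader might infer that every between-arm interval will be too narrow. That needs a positive ICC, which the article does not give, and a contrast that does not remove the group effect, which it does not specify. The WhatsApp group was optional, and nothing shows that colleagues chose the same dates.

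Finally, 4 dates, groups of about 10 and a total of 60 are not strictly contradictory, because a date may have held more than one group. Nor can one assume six randomised dates, since the article says four. Giving availability may also mean marking every feasible date, and the article does not say how such nurses were placed.

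**Conclusion.** The point holds in this limited form and should be fixed. The allocation described makes the date the randomised unit, the Abstract says otherwise, and the stated model has no term for date or group. For exploratory and secondary between-arm comparisons, standard errors are too small whenever there is positive within-date correlation that the tested contrast leaves in place.

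Under assumed ICCs of 0.01 to 0.10 and clustering in both arms, a nominal 5% test would run at about 6.6% to 21% with 15 nurses per date, or about 6% to 15% if correlation acts within groups of 10. At ICC 0 there is no inflation. The direction is firm for any positive ICC that the contrast does not remove; the size rests on these assumptions. The limit of about 2 df for a 2 v 2 split does not depend on the ICC.

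**What to change.** 1. Describe the allocation as randomisation of session dates, and bring the Abstract and the Group Assignment section into agreement. Say how nurses available on more than one date were placed.
2. State how many dates and session groups were in each arm and how they made up the 60 nurses.
3. Account for session date in the between-arm analysis, either with a date term and small-sample degrees of freedom (Kenward-Roger, or dates minus 2) or with a date-level analysis. A date random effect alone is not enough, because its variance is poorly estimated from 4 dates. Name the contrast to be tested.
4. Report these results as estimates with the wider intervals, without significance claims, and note that dates may differ systematically by availability, which no random effect removes with so few units.

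The cost is small: wording and a variable that should already be known for each nurse, while analysis is still in progress (completion is expected around August 2026). The downside is much wider intervals. With 2 df the critical value alone widens them by 4.30/2.00 = 2.15, so formal between-arm inference becomes nearly impossible. That is acceptable for exploratory outcomes in a feasibility pilot.
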